The aim of the project is to evaluate if virtual specialist conferences between endocrinologists and general practitioners about patients living with T2D is clinically effective and improves diabetes competences and organization in general practice in comparison to usual practice. This aim will be studied in a pragmatic randomized controlled trial design that maximizes external validity, is tested in a wide range of participants, and measures important clinical outcomes [25]. Since our intervention will influence the general practice as a whole, it will be the unit of randomization. The intervention was developed using the Medical Research Council (MRC) Framework [26, 27]. The project also studies factors that facilitate or limit the implementation of cross-sectoral and virtual specialist conferences [28], which are important to understand for subsequent upscaling [18]. The project will provide new and clinically relevant knowledge on how to manage the increasing number of persons with T2D seen in general practice.

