### Assignment of interventions

Block randomization is performed at the general practice level. General practices will be randomized in a 1:1 ratio to either the intervention or the control group by a statistician, according to a computer-generated list, independent of the measurement team. Randomization included stratification by number of full-time GPs and geographic location. The latter because general practices located in the centre and periphery of the municipality of Aarhus differ in patient demographics. A hospital secretary will be in charge of enrolment of participants.

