### Outcomes

#### Clinical outcomes

Table 2 shows the primary and secondary patient outcome measures. The primary patient outcomes are the percentage of patients with T2D and three types of co-morbidities on appropriate diabetes-related medication: ischemic heart disease and/or stroke; micro- or macro-albuminuria; and LDL > 2.5 mmol/L. To account for multiplicity, we use the Bonferroni correction method to adjust the *p*-values of the three primary clinical outcomes. The Bonferroni correction sets the significance cut-off at α/n [36], which means we only reject the null hypothesis of a primary clinical outcome if the *p*-value is less than 0.0167 (i.e., 0.05/3).

**Table 2 Tab2:** Overview of primary and secondary outcomes measures

Aspect	Outcome measure
Primary clinical outcome measures	Percentage of patients with T2D and ischemic heart disease and/or stroke being treated with glucagon-like peptide 1 receptor agonists (GLP1-RA) and sodium glucose cotransporter 2 (SGLT2) inhibitor
	Percentage of patients with T2D and micro/macro-albuminuria being treated with angiotensin-converting-enzyme-inhibitor (ACE) or angiotensin-2-receptorantagonist (AT2)
	Percentage of patients with T2D and LDL > 2.5 mmol/L being treated with statins
Secondary clinical outcome measures	Percentage of patients with T2D and HbA1c < 58 mmol/L
	Percentage of patients with T2D and HbA1c < 53 mmol/L
	Percentage of patients with T2D and blood pressure < 140 mmHg
	Percentage of patients with T2D and blood pressure < 130 mmHg
	Percentage of patients with T2D and low-density lipoprotein > 2.5 mmol/L
	Percentage of patients with T2D and microalbuminuria and LDL > 1.8 mmol/L
Primary competence and organization outcome measures	The extent to which the GP is confident managing T2D in general
	The extent to which the GP is skilled in making decisions on T2D in general
	The extent to which the GP is confident managing T2D and ischemic heart disease, stroke, peripheral artery disease, and heart failure
	The extent to which the GP is confident managing T2D and blood pressure
	The extent to which the GP is confident managing T2D and kidney disease
	The extent to which the GP is confident managing T2D and cholesterol
Secondary competence and organization outcome measures	GPs rating of the degree of relational coordination within the general practice
	GPs rating of the degree of relational coordination with the endocrinology department

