#### Clinical outcomes

Clinical outcomes will be collected from an IT-platform (DEN: “Diabetes Overblik”. ENG: “Diabetes Overview”) used by Danish general practices, which contains anonymous and aggregated diabetes data about patients (Additional file 3 shows screenshots). As per the agreement to participate in the study, each general practice assigns a contact person who will e-mail the screenshot of the data to the project group. Each general practice is renumerated for performing this activity. Data will also be obtained from nationwide Danish registries: The Clinical Laboratory Information System Research Database (LABKA), The Danish National Prescription Registry (DNPR), The Danish National Health Service Register (NHSR), The Danish Civil Registration System (CRS), and The Danish National Patient Register (NPR). Register data will be linked to the unique provider number of each general practice.

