### Sample and power calculation

The pragmatic nature of the RCT means that the sample size is determined by two contextual circumstances: a formal agreement with PLO-Aarhus and PLO-M to run the study in Aarhus Municipality (cf. above) where the total population of general practices was 100 and the fact that Danish general practices operate as private firms and thus decide themselves if they want to participate in a project. Based on these circumstances along with the study team’s research experiences with recruiting general practices, we used opinion-seeking to derive at the number of 30 general practices that were expected to participate.

We calculated the power for finding a significant difference between the intervention and control group on the three primary clinical outcomes using data from Danish registries and opinion-seeking within the study team. Additional file 5 shows the key parameters and the STATA command we used to calculate the following three power values:Power of 0.8870 for Primary clinical outcome 1: Percentage of patients with T2D and ischemic heart disease and/or stroke being treated with GLP1-RA and SGLT2 inhibitorPower of 0.9941 for Primary clinical outcome 2: Percentage of patients with micro/macro-albuminuria being treated with ACE or AT2Power of 0.9848 for Primary clinical outcome 3: Percentage of patients with LDL > 2.5 mmol/L being treated with Statins.

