#### Difference between intervention and control group

The main analysis concerns the difference between the intervention and control group at month 12. Data from the Diabetes Overview and general practice survey are analysed using simple, multiple, and logistic regression analyses. Analysis is done according to the intention-to-treat principle to test if the groups differ in terms of outcome measures. The analysis of survey data will take into account cluster effects using the intra-cluster correlation coefficient. Using *t*-test and *Χ*^2^ tests, depending on the outcome measure, it will be determined if randomization has resulted in systematically different groups. Survey data are tested to determine if questions or indices of questions are internally consistent (Cronbach alpha). In the regression analyses, control variables at the individual (e.g., seniority) and practice level (e.g., form and size of practice) are tested to determine its influence on survey outcomes.

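### Practices are randomised, but clustering is provided for only in the survey analysis and no unit of analysis is fixed for the three primary clinical outcomes, so a test that ignores practice would comply with the plan

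*Protocol article*

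**What the plan says.** All references are to the protocol article.

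- Background: "Since our intervention will influence the general practice as a whole, it will be the unit of randomization". Assignment of interventions repeats this: "General practices will be randomized in a 1:1 ratio to either the intervention or the control group".
- Sample and power calculation: opinion within the study team was used to "derive at the number of 30 general practices that were expected to participate". The abstract gives 15 per arm.
- Outcomes, Clinical outcomes: "The primary patient outcomes are the percentage of patients with T2D and three types of co-morbidities on appropriate diabetes-related medication". Each of the three is tested at 0.05/3 = 0.0167.
- Data collection, Clinical outcomes: the main source is the Diabetes Overview, "which contains anonymous and aggregated diabetes data about patients". Each practice e-mails a screenshot. Data from five national registries, linked by the practice's provider number, are to be obtained as well.
- Statistical analysis plan, Difference between intervention and control group: "Data from the Diabetes Overview and general practice survey are analysed using simple, multiple, and logistic regression analyses". Later in the same paragraph comes the only provision for clustering: "The analysis of survey data will take into account cluster effects using the intra-cluster correlation coefficient".

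No section names a unit of analysis, a practice effect or a cluster adjustment for the clinical outcomes.

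**The concern.** Patients of one practice share doctors, prescribing habits and case mix, so their treatment status is correlated. When practices are randomised, the arm comparison must be judged against the variation between practices. A model that treats patients as independent gives standard errors that are too small and tests that reject too often.

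The analysis section deals with clustering explicitly but confines it to the survey. It also lists logistic regression for a pair of sources that includes the one holding the primary outcomes. Survey answers are on a 1 to 5 scale, whereas the clinical outcomes are yes/no at patient level, so logistic regression is at least as natural for the clinical outcomes as for the survey. A statistician following this text could fit a binomial logistic model to numbers treated out of numbers eligible, with no practice effect, and be within the plan.

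At stake are all three confirmatory clinical tests. The Bonferroni rule would not help in that case: it divides alpha across three tests but does not repair a test that misses its own nominal level.

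**Working it through.** **The plan's own figures.** 0.05/3 = 0.0167 reproduces. The stated powers (0.8870, 0.9941, 0.9848) cannot be reproduced, because their inputs are in Additional file 5, which is not shown. Nothing below relies on them.

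**Inputs from the article.** 15 practices per arm; two-sided tests; alpha 0.0167 per primary clinical outcome, so the critical value is 2.394.

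**Assumed inputs.** Eligible patients per practice and outcome, m = 15 to 60; intra-cluster correlation (ICC) 0.01 to 0.05. For scale only, the article's national figures give 240,000/3,326 = about 72 patients with type 2 diabetes per GP. That does not fix the size of the three subgroups.

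**Formulas.** Design effect DE = 1 + (m − 1) × ICC. True two-sided type I error of a test that ignores practice = 2 × [1 − Φ(2.394/√DE)].

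**Worked cases.**
- m = 15, ICC 0.01: DE = 1 + 14 × 0.01 = 1.14; 2.394/1.068 = 2.242; error 0.025.
- m = 30, ICC 0.05: DE = 1 + 29 × 0.05 = 2.45; 2.394/1.565 = 1.530; error 0.126.
- m = 60, ICC 0.05: DE = 1 + 59 × 0.05 = 3.95; 2.394/1.987 = 1.205; error 0.228.

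Type I error at nominal 0.0167, with the design effect in brackets:

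| m | ICC 0.01 | ICC 0.02 | ICC 0.05 |
|---|---|---|---|
| 15 | 0.025 (1.14) | 0.034 (1.28) | 0.066 (1.70) |
| 30 | 0.035 (1.29) | 0.057 (1.58) | 0.126 (2.45) |
| 60 | 0.058 (1.59) | 0.105 (2.18) | 0.228 (3.95) |

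**Simulation check.** 20,000 null trials per setting, 15 against 15 practices, unequal practice sizes with mean 30 or 60, underlying rate 0.5, beta-binomial outcomes. Two tests at nominal 0.0167 were compared: a pooled two-proportion test, which corresponds to logistic regression with arm as the only term, and a t-test on the 30 practice percentages.

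| Mean m | ICC | Pooled test | Practice-level t-test |
|---|---|---|---|
| 30 | 0.01 | 0.041 | 0.015 |
| 30 | 0.05 | 0.153 | 0.017 |
| 60 | 0.01 | 0.066 | 0.016 |
| 60 | 0.05 | 0.265 | 0.018 |

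Unequal practice sizes make the pooled test somewhat worse than the formula (0.153 against 0.126 at m = 30, ICC 0.05). Over all settings run, with ICC from 0 to 0.10, the practice-level test stayed between 0.014 and 0.019.

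**The case against.** The best defence is the form of the data. The Diabetes Overview is aggregated, each practice sends a screenshot, and the Discussion again describes the primary and secondary outcomes as screenshots. The natural data set is then one percentage per practice, about 30 rows, with the unit of analysis equal to the unit of randomisation and no within-practice correlation left to model. The survey is different, because several GPs and staff answer in each practice. On this reading, mentioning cluster effects for the survey alone is just what one would write. Further, logistic regression is listed jointly for two sources and is not assigned to the primary outcomes; the main-analysis section does not name the registry data; and a separate analysis plan or Additional file 5 may settle the unit.

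Much of this stands. It defeats the stronger reading that a reader might infer, namely that the confirmatory analysis is invalid as planned and its p-values wrong. The documents do not commit to an unadjusted analysis, and one of the listed methods, linear regression on practice percentages, is sound.

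It does not close the point. Logistic regression is not limited to the survey. If the screenshots show numerators and denominators, a grouped logistic model is possible and treats patients as independent. The registry data are listed as a source for clinical outcomes, and no clustering provision reaches them. Nor is this merely detail deferred to an analysis plan: the article does state a clustering rule, and states it for the survey only.

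**Conclusion.** The concern holds as a conditional one. The plan admits both a valid and an invalid analysis of its three primary clinical outcomes and does not choose between them. If patient counts or patient records are analysed without a practice effect, each test nominally at 0.0167 would have a true type I error of about 0.025 to 0.23, roughly 1.5 to 14 times nominal (0.025/0.0167 and 0.228/0.0167). That range rests on the assumed 15 to 60 patients per practice and ICC of 0.01 to 0.05, and the excess is modest at the low end. If the practice percentages are analysed, the error stays close to nominal.

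Two further inferences are not supported. A combined false-positive rate over the three outcomes should not be computed as if they were independent: they come from the same practices and can share patients. And it cannot be said that the power calculation ignored clustering, since its inputs are not shown.

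**What to change.** In the section on the difference between intervention and control group, state that every between-arm analysis of clinical outcomes respects the general practice as the randomised unit, and name the model:

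- for the aggregated Diabetes Overview data, a linear regression on the practice-level percentages, with a t reference distribution and practice-level degrees of freedom; or
- if patient counts or patient-level registry records are used, a mixed logistic model with a random practice intercept and a small-sample correction suited to about 30 clusters.

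Extend the clustering provision beyond the survey, and state that logistic regression without a practice effect will not be used for these outcomes.

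This is a change of wording only, with no new data and no effect on recruitment. If a practice-level analysis was always intended, a sentence saying so is enough and nothing else changes. If an unadjusted analysis was intended, the confidence intervals become wider and power falls accordingly.

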#### Outcomes, process measures, and changes in the individual arms

The two groups (intervention and comparison arms) are analysed on their own using data from the process measures and organizational changes during the study period. The starting point of the intervention group is compared with the outcome measures when the intervention ends (months 0 to 12) and again when the maintenance phase ends (months 12 to 24) to examine the maintenance effect. The intervention period of the control group (months 12 to 24) is analysed to determine the intervention effect. The analyses of the two individual arms are used to study internal changes (before vs. after) and to study if the process measures can explain why the two groups achieve the results they do.

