## Introduction

### Background

Globally, 462 million people is estimated to live with type 2 diabetes (T2D). This corresponds to 6.3% of the world’s population, which makes T2D one of the most common chronic diseases [1]. In Denmark, 240,000 people (4.1%) are diagnosed with T2D, and by 2030, the number is projected to nearly double [2]. T2D elevates the risk of developing macro- and micro-vascular complications (e.g., atherosclerotic cardiovascular disease, chronic kidney disease and peripheral neuropathy) resulting in higher mortality, higher morbidity, increased disability, poorer quality of life [3], and a substantial economic burden for society in medical costs and reduced productivity [4]. The risk of developing complications can be considerably reduced if health care professionals help to secure optimal levels of lipids, blood pressure, and glycated haemoglobin by appropriate pharmacological treatment to supplement life-style interventions [3, 5]. However, management of T2D is a complex task since it is often accompanied by other diseases (e.g., heart or kidney failure) [6–8], which requires the use of several different and sometimes interacting drugs. Furthermore clinical guidelines are revised regularly as new knowledge and new pharmaceuticals emerge at a rapid pace [9, 10]. Unfortunately, these care challenges have led to a wide gap between the recommended pharmacological care and the care that patients receive, both internationally and in Denmark [11–13]. Thus, it is urgent to improve the pharmacological management of patients living with T2D.

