Conferences and webinars are carried out according to a manual. The intervention will not be modified during the study period. The general practices in the intervention group will transition to a maintenance phase (month 12 to 24) where they get a maximum of two virtual specialist conferences.

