#### Comparison arm

General practices allocated to the control group will continue to get access to the usual written or telephone support by an endocrinologist in hospitals. This requirement to provide diabetes support to GPs is part of a collective agreement between the Danish Regions and the Association of General Practitioners [35]. The control group will get the intervention after the primary intervention ends, that is, after month 12.

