### Data collection

Table 3 shows the study schedule including data collection points according to the SPIRIT guideline. Data are collected at month 0, 12, and 24 for the intervention group and month 12 and 24 for the control group.

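### The former control arm's month 12 to 24 before-after change is meant to show the intervention effect, but no unexposed comparator exists in that period

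*Protocol article*

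**What the plan says.** The protocol article, under Outcomes, process measures, and changes in the individual arms, gives the second-period analysis of the controls a causal purpose: "The intervention period of the control group (months 12 to 24) is analysed to determine the intervention effect". The same paragraph opens with "The two groups (intervention and comparison arms) are analysed on their own", and its last sentence adds: "The analyses of the two individual arms are used to study internal changes (before vs. after").

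Three other sections fix what can be compared in that period:

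- Comparison arm: "The control group will get the intervention after the primary intervention ends, that is, after month 12".
- Intervention arm: those practices "will transition to a maintenance phase (month 12 to 24) where they get a maximum of two virtual specialist conferences".
- Data collection: "Data are collected at month 0, 12, and 24 for the intervention group and month 12 and 24 for the control group".

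Under Difference between intervention and control group, the main analysis is the between-arm comparison at month 12.

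**The concern.** A change within one arm, without a concurrent unexposed group, measures the intervention together with everything else that happened over the same year. The article gives reasons to expect other things to happen. Its Background says that "new knowledge and new pharmaceuticals emerge at a rapid pace". Its Discussion, in the limitation on blinding, accepts that control practices may improve their diabetes care on their own initiative.

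The Discussion also describes a measurement effect. At the introductory session GPs review their list of diabetes patients, adding and removing patients and checking diagnostic codes. The controls receive the intervention after month 12, so their month-12 value comes before that review and their month-24 value after it. The clinical outcomes are percentages of listed patients, so the denominator can move without any change in prescribing.

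The stake is what the trial may conclude about its second year. The Dissemination plan expects an analysis after each intervention period, so this result will be produced. With the present wording it could be reported as an effect of the conferences.

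**Working it through.** The article states no figure for this analysis, so there is none to reproduce. The three powers under Sample and power calculation concern the comparison of intervention and control groups, and their inputs are in Additional file 5, which is not shown.

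**Is there a comparator in months 12 to 24?**

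| Question | What the article gives |
|---|---|
| Is the analysed arm exposed? | Yes, from month 12 (Comparison arm) |
| Is the other arm unexposed? | No. It has had four conferences and may have up to two more (Intervention arm) |
| Is there an earlier trend for the controls? | Not from the scheduled trial collection, which starts at month 12 for them (Data collection) |
| Is a trend adjustment or external comparator named for this analysis? | No |

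Register data are also to be obtained (Data collection, Clinical outcomes) and could hold earlier values, but the article does not assign them to this purpose.

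**Bias.** Let *e* be the true effect of the conferences, *g* the change over months 12 to 24 that would have happened without them, and *d* the change caused by the list review alone. Then

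E(month 24 − month 12) = *e* + *g* + *d*, so bias = *g* + *d*.

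This needs no assumed figure.

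**Illustration of the consequence.** Assumptions, none of them in the documents: *e* = 0, *d* = 0, a one-sample t-test on practice-level changes, and an SD *s* of those changes of 5, 10 or 15 percentage points. The number of control practices, 15, is the planned number in the Abstract.

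SE = *s*/√15, and the noncentrality is *g*/SE on 14 degrees of freedom. For *g* = 5 and *s* = 10: SE = 10/3.873 = 2.582, and the noncentrality is 5/2.582 = 1.94. Against a two-sided 0.05 critical value of 2.145, the rejection probability is 43.8%.

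Probability of a significant result when the conferences do nothing:

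| Two-sided level | SD of change | *g* = 2 | *g* = 5 | *g* = 10 |
|---|---|---|---|---|
| 0.05 | 5 | 30.3% | 94.9% | about 100% |
| 0.05 | 10 | 11.2% | 43.8% | 94.9% |
| 0.05 | 15 | 7.7% | 22.5% | 67.1% |
| 0.0167 | 5 | 15.9% | 85.8% | about 100% |
| 0.0167 | 10 | 4.6% | 25.7% | 85.8% |
| 0.0167 | 15 | 2.9% | 10.9% | 47.0% |

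The level 0.0167 is the article's Bonferroni threshold, 0.05/3. The article does not say whether it applies to this analysis, so both levels are shown.

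**What a concurrent comparator would do.** A simulation of 20,000 runs set 15 practices against 70 unexposed ones, with SD 10, *e* = 0 and the same *g* in both groups. The 70 is 100 invited practices minus the 30 expected to take part.

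| *g* | Before-after: bias | Before-after: rejection | Controlled: bias | Controlled: rejection |
|---|---|---|---|---|
| 0 | −0.03 | 4.9% | −0.05 | 4.7% |
| 2 | 2.01 | 10.9% | 0.00 | 5.0% |
| 5 | 5.02 | 43.9% | 0.02 | 5.0% |
| 10 | 10.00 | 94.9% | 0.00 | 4.8% |

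The trend cancels because both groups were given the same one. The simulation does not show that real non-participating practices would share it.

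**The case against.** The strongest reply is that the article already discloses what this analysis is. The section title refers to changes in the individual arms, the arms are said to be analysed separately, and the closing sentence speaks of internal change before and after. The hierarchy is also clear: the month-12 between-arm difference is the main analysis, and nothing says that the second-period change replaces it or is pooled with it. This stands, and it limits the weight of the point. It does not remove it, because the closing sentence softens the causal purpose without withdrawing it.

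Some data collection helps interpretation. The GP survey records other contacts with the hospital (Concomitant hospital support), and control practices are asked about changes made in the past year (Discussion). Neither separates a time trend from an effect.

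Four stronger readings are tempting, and the documents do not support them:

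- *Growth in newer drugs will be credited to the conferences.* No rate of growth is given. The Background passage on rapid change goes on to describe care lagging behind recommendations, so the size and even the sign of any trend are open. The mechanism also fits mainly the first primary clinical outcome (GLP1-RA and SGLT2 inhibitor); the other two concern ACE/AT2 drugs and statins.
- *The trial's main result is compromised.* The month-12 analysis is a separate, randomised contrast and does not use this change.
- *The intervention arm's month 0 to 12 change is also presented as an effect.* The article describes it only as a comparison of the starting point with the end of the intervention.
- *The second period will be used to rescue a null result.* That is conjecture about reporting; no such use is planned.

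**Conclusion.** The point holds as a fault in the stated purpose of one supplementary analysis. The month 12 to 24 change in the former controls cannot determine the intervention effect, because no trial arm is unexposed in that period and the scheduled collection gives the controls one measurement before and one after.

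The bias is exactly the background change plus any list-review shift. It can go in either direction: it can create an apparent effect or hide a real one. Its size cannot be derived from the documents. On the assumed values, false-positive rates at two-sided 0.05 run from 8% (2 points, SD 15) to nearly 100% (10 points, SD 5). Those figures depend on the assumed trend, SD and test; the bias identity does not.

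The weight is moderate. The change is worth making because it governs what may be concluded from the second year.

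**What to change.** In the section on changes in the individual arms, replace the purpose clause on the control group's second period with wording that the analysis describes within-arm change. Add a statement that the randomised month-12 comparison is the only estimate of the intervention effect, and that all within-arm changes (months 0 to 12 and 12 to 24, in either arm) are descriptive.

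The cost is wording only. The downside is a weaker claim for the second year.

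If the investigators still want an effect estimate for that period, it needs an outside reference: either the earlier trend in the same practices from the registers, or the concurrent change in non-participating Aarhus practices. This is optional. It depends on data access that the article does not confirm. It must be labelled non-randomised, with its parallel-trends assumption stated. For non-participating practices that assumption is doubtful, since the Discussion itself warns that participants may be unusually interested in diabetes.
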